## Abstract

**Background:**

Subthreshold depression is common in primary care and is associated with significant healthcare burden. There is emerging evidence for the benefits of Exercise can reduce depressive symptoms among people with diagnosed depression, but there is limited evidence for subthreshold depression in primary care setting. This study aims to examine the efficacy of a 12-week online instructor-led exercise intervention in reducing depressive symptoms among people with subthreshold depression in primary care, when compared to usual care control.

**Methods:**

This 1:1 randomised controlled trial will enrol 260 participants with subthreshold depression randomizing into 2 groups (online exercise intervention versus usual care control). The intervention consists of twice-weekly 1-h exercise online classes over 12 weeks, which will be led by certified instructors. Data will be collected at baseline (T0), immediate post intervention (T1), 3-month post intervention (T2) and 9-month post intervention (T3). The primary outcome is depressive symptoms measured by the Chinese version of Beck Depression Inventory-II (BDI-II) at T1. Secondary outcomes include anxiety symptoms, quality of life, physical activity levels, feasibility and acceptability, medication use and health service utilization, and cost assessment. Intention-to-treat analysis will be performed.

**Discussion:**

The proposed study will assess the efficacy of online exercise intervention in improving subthreshold depressive symptoms in primary care. The findings will inform clinicians and policy makers concerning prevention of depression in primary care, and may lead to changes in the respective current guidelines and public policies.

**Trial Registration:**

This trial has been registered in the Chinese Clinical Trial Registry, with the registration number: ChiCTR2400087923. The date of registration is 2024–08-07.

**Supplementary Information:**

The online version contains supplementary material available at 10.1186/s12888-025-06663-0.

## Introduction

### Background

Subthreshold symptoms that do not fulfil the diagnostic criteria for major depression are common in primary care [1] and are associated with significant healthcare burden [2]. People with subthreshold depression are at high risk for developing major depression with an incidence of 18%, three times as much as that in the general population [3]. In addition, up to 60% may have a chronic course with 25% developing into a more severe form of depression [4]. Therefore, evidence-based interventions that can be readily implemented in primary care are needed.

At present, cognitive behavioural therapy (CBT) or CBT-based problem-solving therapy is the most evidence-based interventions for people with subthreshold depressive symptoms [5]. However, there is often a long waiting time for CBT-based interventions in the public sector while the cost for psychotherapy can be prohibitive in the private sector. Moreover, people at increased risk for depression including older adults and people of disadvantaged background may either lack the cognitive skills or the time needed for CBT [6]. On the other hand, primary care providers may find CBT training and interventions too time consuming. As the demand for evidence-based psychological interventions is far greater than services available in Hong Kong, a simple and implementable preventive intervention for managing depressive symptoms is urgently needed.

It is well established that physical exercise is beneficial to health. Evidence shows that exercise can improve mood and reduce depression and anxiety in addition to physical health benefits [7]. A recent large overview of 97 systematic reviews on the effectiveness of exercise interventions for improving depression, anxiety and psychological distress showed that exercise can improve depressive symptoms across various adult populations including older adults and people with depressive symptoms, demonstrating a moderate to large effect size similar to that of psychotherapy and pharmacotherapy [8].

Despite the well-proven health benefits of exercise, physical inactivity is common. A recent Hong Kong survey shows that about 25% of adults aged 18 or above had insufficient physical activity according to the World Health Organization (WHO) recommendation [9]. Moreover, there is a significant increase in the prevalence of physical inactivity when compared to findings from a previous survey [10]. Among people with chronic conditions including depression, only about 25% participate in regular physical activities.

The WHO has recommended reducing physical inactivity as one of the “best buy” policies in tackling non-communicable diseases [11]. However, patients face significant barriers to engage in physical activity including lack of knowledge, skills and resources (e.g. venue and materials for exercise) [12, 13], lack of social support [13], receiving non-specific instructions from health care professionals (for patients) [12] and not considering physical exercise as important [12]. From the theory of behavioural economics [14], people's preferences are highly malleable and seemingly trivial contextual factors such as availability of venues, or the presence of simple feedback can have substantial influence on people’ health behaviours. This is supported by research showing that effects from facilitated physical activity based on health coaching alone using physical activity facilitators (no physical trainers to provide instructions or skills transfer) may not be large enough to produce clinically significant effects on depressive symptoms [15]. Simple behavioural techniques [16] such as instruction on how to perform a behaviour, followed by feedback on behaviours and the provision of a clear pathway in identifying context, frequency, duration and intensity of the required behaviours can all substantially result in positive changes of desirable behaviours and improvement of health outcomes.

Previously, a clinical trial was conducted to examine the effectiveness of a complex exercise programme, named the “Exercise Is Medicine” (EIM) programme, in normalizing the nocturnal blood pressure of hypertensive patients in Hong Kong [17]. Due to the social restriction policy implemented in Hong Kong during the peak of COVID-19 pandemic, part of the EIM programme was delivered through the Zoom online platform. Although depressive symptoms were not the outcome of the study, such symptoms (in the form of Patient Health Questionnaire depression scale [PHQ-9] [18]) were measured for all participants. Fifty-four people with mild depressive symptoms at baseline received online exercise intervention. Class attendance rate was 90.4% while dropout rate at 12 month follow up was 13%. The preliminary results (yet to be published, by courtesy of the authors) showed a significant decrease of mean PHQ-9 score from 6.7 at baseline to 3.8 at 12 months after recruitment (95% confidence interval for the mean difference was −4.1, −1.7). Although these preliminary findings are encouraging, the exploratory nature and small sample size resulted in limited internal validity. A properly designed randomised controlled trial is therefore needed to examine the programme’s efficacy in reducing depressive symptoms among patients with subthreshold depression when compared to a control group.

Furthermore, while there are a number of trials evaluating the cost-effectiveness of various internet-based interventions for the management of depression [19], none of the trials included online exercise programme in their intervention arms. Thus, a new study focusing on an internet-based, structured exercise intervention is needed to provide data for preliminary cost assessment and insights into the cost-effectiveness of such intervention in primary care setting.

### Objectives and Hypotheses

The primary objective of the study is:

To examine the efficacy of a 12-week online instructor-led exercise intervention (EIM) when compared to usual care control in reducing depressive symptoms among people with subthreshold depression in primary care.

The secondary objectives of the study are:To examine the efficacy of a 12-week online instructor-led exercise intervention (EIM) when compared to usual care control in reducing anxiety symptoms and improving quality of life among people with subthreshold depression in primary care; andTo examine the cost-effectiveness of the intervention.

The hypotheses of the study are:The online instructor-led exercise intervention will be more effective when compared to usual care in reducing depressive symptoms among patients with subthreshold depression (primary hypothesis);The online instructor-led exercise intervention will be more effective in reducing anxiety symptoms and improving quality of life when compared to usual care (secondary hypothesis); andThe online instructor-led exercise intervention will be a cost-effective intervention in primary care (secondary hypothesis).

## Methods

### Study design

This will be a pragmatic randomized controlled trial with two arms: online instructor-led exercise intervention versus usual care control in primary care. Assessments will be conducted at baseline (T0), immediate post intervention (T1), 3-month post intervention (T2) and 9-month post intervention (T3). An overview of the study design is shown in Fig. 1.

**Fig. 1 Fig1:**
[figure not shown]
Schematic overview of the study. Caption: Participants will be randomized into online exercise programme group and control group. Assessments will be conducted at baseline (T0), immediate post intervention (T1), 3-month post intervention (T2) and 9-month post intervention (T3)

### Participants

The following inclusion and exclusion criteria will be used to determine the eligibility of the participants.

The inclusion criteria are: (1) aged 18 years or above; and (2) having subthreshold depression as defined by having a score 5–9 on the Patient Health Questionnaire depression scale (PHQ-9) [18], i.e., having a total score of 5 to 9 inclusive.

The exclusion criteria are: (1) dysthymia with subthreshold depressive symptoms that last for 2 years or more; (2) major depression within the past 6 months; (3) lifetime history of other psychiatric disorders (including but not limited to generalized anxiety disorder, schizophrenia, bipolar affective disorder and substance use disorder); (4) current use of antidepressant; (5) currently enrolled in any form of psychological interventions for any depressive symptoms; (6) medical illness with a prognosis of less than 6 months to live; and (7) recently diagnosed or uncontrolled cardiovascular, metabolic or neurological conditions.

### Study setting and recruitment

Participants will be recruited from public primary care clinics, i.e., General Outpatient Clinics (GOPCs) and Family Medicine Clinics (FMCs) of the New Territories East Cluster (NTEC) of Hong Kong. Currently, GOPCs and FMCs in NTEC serve a population of more than 1 million residents, resulting in a high representativeness. Apart from GOPCs and FMCs, recruitment will also be conducted in collaboration with non-governmental organizations, which will refer individuals with primary care needs in the community.

### Intervention: Online exercise programme

The design of the exercise class (duration and frequency) is modified from the class for diabetes and hypertension based on findings from recent systematic reviews on the effectiveness of physical activity intervention for improving depression and anxiety [8]. The 12-week EIM program aims to transform participants' exercise habits by fostering and maintaining behavioural changes through motivation, as well as providing relevant knowledge and experience. The online classes will be conducted by certified physical trainers who hold a post-secondary degree (or equivalent), possess a valid basic life support certificate, and have been certified by the Physical Fitness Association of Hong Kong after passing examinations. They have also completed specialized training to deliver the EIM program.

The 12-week EIM online class on the Zoom platform (details in Appendix 1) will enrol 11 to 18 patients per group and meet twice a week for 1 h each time. Each class contains a set of exercises including stretching, aerobic exercise and resistance training (combined exercise) and will be carried out according to specific protocol [17] (Appendix 1). Participants will receive reminders about each session via WhatsApp or telephone calls. After each class, home exercises were assigned to achieve a minimum of 150 min of exercise per week. Additionally, regular SMS or WhatsApp messages will be sent to remind and encourage participants to incorporate exercise into their daily routines. Furthermore, participants will also be provided with smartwatches to track their physical activities. The trainers can monitor participants' activity levels via trackers before each lesson, enabling them to motivate individuals and address barriers as needed, thereby offering regular reinforcement, social support, and problem-solving assistance. Zoom lessons will be recorded, and approximately 15% of these recordings will be reviewed by the investigator to ensure fidelity to the intervention.

### Care as usual control

Participants in the both groups have unrestricted access to GOPCs for any health problem, including depressive symptoms. In Hong Kong, the general outpatient clinics provide primary care services at a low subsidized fee.

Participants assigned to the control group will receive medical care from GOPCs. In Hong Kong, individuals with subthreshold depression are managed in primary care setting instead of being referred to mental health specialists.

### Randomization, concealment and blindness

Stratified randomization will be used to enhance balance of gender, anxiety symptoms (“minimal to mild” versus “moderate to severe” as classified by the Beck Anxiety Inventory [21]) and level of physical activity (“low”, “medium” and “high” as classified by the International Physical Activity Questionnaire – Short Form [23]) at baseline between two arms. The randomisation procedure will be conducted by an independent statistician. Participants will be individually notified of the randomization results via phone or WhatsApp messages by a research assistant. Outcome assessors will be blinded from the group assignment. Due to the characteristics of the intervention, researchers and participants cannot be blinded after group allocation.

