### Sample size

From a previous trial on assessing the efficacy of group-based behavioural activation with mindfulness for treating subthreshold depression in primary care in Hong Kong, mean (standard deviation) of BDI-II score at baseline for intervention and usual group were 19.18 (8.35) and 17.68 (9.52) respectively among participants with subthreshold depression. Pooled mean and standard deviation were 18.43 and 8.95 from two groups. For moderate baseline severity, the minimum clinically important difference (MCID) on the BDI-II was estimated at 3.5 points [24]. Assuming at least the MCID could be seen in the online exercise programme at 4-month post randomisation compared to usual care, sample size of 104 each group achieve 80% power to detect the difference of 3.5 points in BDI-II with a common standard deviation of 8.95 at a significance level of 0.05 using two-sided t-test. The corresponding effect size of 0.39 is similar to the finding from a systematic review that physical activity is beneficial for improving depressive symptoms with effect size of 0.43 [8]. From our experience in running online exercise intervention for people with subthreshold depression, a dropout rate of 13% at 12 month follow up was observed. To be conservative, we assume drop out to be 20%, and set our enrolment target at participants in total of 260 with 130 participants in each group.

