### Statistical analysis

Baseline characteristics of the two groups will be compared using chi-square test for categorical variables and independent samples t-test for continuous variables. Analysis of covariance (ANCOVA) for the BDI-II score at T1 will be conducted as the primary analysis, with the BDI-II score at T0 and other characteristics with significant between-group difference at T0 as covariates in the model for sensitivity analyses. Effect size estimates will be obtained for the primary outcome, with the between group effect sizes (Cohen’s d) being calculated using the mean differences from baseline and the SDs of the two groups at each time point. For the secondary analysis, linear mixed models (LMM) with random intercept will be applied to investigate the significant changes over time, for both primary and secondary outcome measures. The LMM approach is in line with the intention-to-treat principle, to include all subjects for the analysis and use all available data to assess the treatment effect over time. Maximum likelihood estimation (MLE) will be employed to handle missing data in the analyses with LMMs. A sensitivity analysis will be conducted using imputed data generated by multiple imputation. Furthermore, compliance with prescribed exercises will be added into the models to explore if this is predictor of changes in health outcomes.

In the cost-utility analysis, utility will be measured with quality adjusted life years (QALYs) based on SF-12 using the Hong Kong weights. The area under curve approach will be used to calculate the utilities at follow-ups after adjusting for baseline utility. In the cost-effectiveness analysis, remission of depressive symptoms (BDI-II score of < 14) will be used as outcome. Using both provider and societal perspectives, incremental cost-effectiveness ratio (ICER) will be calculated by dividing cost difference of two groups by between-group effect difference. We will use bootstrapping technique to assess the uncertainty of the ICER estimate. Due to the lack of a local willingness-to-pay threshold, we will generate cost-effectiveness acceptability curves to evaluate the probability of cost-effectiveness of the proposed intervention.

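### The stated covariate rule in effect keeps the stratification factors out of the ANCOVA, which makes the primary test mildly conservative if those factors are prognostic

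*Protocol article*

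**What the plan says.** Under Randomization, concealment and blindness, the protocol article says: "Stratified randomization will be used to enhance balance of gender, anxiety symptoms". Anxiety has two classes on the Beck Anxiety Inventory (BAI). The third factor is physical activity in three levels, "as classified by the International Physical Activity Questionnaire – Short Form [23]) at baseline between two arms". With gender this makes 2 × 2 × 3 = 12 strata.

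Under Statistical analysis: "Analysis of covariance (ANCOVA) for the BDI-II score at T1 will be conducted as the primary analysis". The same sentence gives the covariates as the T0 BDI-II score and "other characteristics with significant between-group difference at T0 as covariates in the model for sensitivity analyses". No stratification factor is named. For the secondary analysis, "linear mixed models (LMM) with random intercept will be applied to investigate the significant changes over time"; no fixed-effect covariates are listed or ruled out.

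The Sample size section uses an unadjusted two-sided t-test, with "80% power to detect the difference of 3.5 points in BDI-II with a common standard deviation of 8.95".

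**The concern.** The design and the covariate rule work against each other. A stratification factor could enter the ANCOVA only by showing a significant difference between arms at T0, and stratification exists to prevent that difference. The factors thought important enough to balance are therefore the ones least likely to be adjusted for.

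Stratified allocation removes between-stratum variation from the real sampling error of the treatment difference. A model without the strata leaves that variation in its residual. If the factors are prognostic, its standard error is then too large, the confidence interval too wide and the test conservative.

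The rule is also weak in itself. A baseline significance test in a randomised trial does not identify prognostic variables, and it leaves the adjusted model to be settled after data have been seen.

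**Working it through.** **Inputs from the protocol article.** Difference 3.5 points, SD 8.95, two-sided alpha 0.05, 104 per group analysed, 20% dropout, 260 randomised 1:1 (Sample size); 12 strata (Randomization).

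**Inputs assumed, because the article does not give them.** R², the share of T1 BDI-II variance that the strata explain beyond T0 BDI-II: 0 to 0.20. Correlation rho between T0 and T1 BDI-II: 0 (no baseline adjustment) or 0.5.

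**The plan's own figure.** The exact t-test solution is 103.6, so 104 per group, with power 0.801. Dropout: 104 / 0.80 = 130 per group, 260 in total. Both figures reproduce.

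**Formulas (normal approximation, near-exact balance of strata in the analysed sample).** Let k = √(1 − R²), se = 8.95 × √(1 − rho²) × √(2/104), and ncp = 3.5/se.

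- Factor by which the reported standard error is too large when strata are omitted: 1/k
- True type I error, strata omitted: 2Φ(−1.96/k)
- Power, strata omitted: Φ((ncp − 1.96)/k)
- Power, strata included: Φ(ncp/k − 1.96)

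For rho = 0, se = 8.95 × √(2/104) = 1.241 and ncp = 2.820. Power at R² = 0 is Φ(0.860) = 80.5%. For rho = 0.5, se = 1.075 and ncp = 3.256, which gives 90.3%.

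Worked line, R² = 0.10 and rho = 0: k = 0.949. Type I error = 2Φ(−2.066) = 3.9%. Power omitted = Φ(0.860/0.949) = 81.8%. Power included = Φ(2.820/0.949 − 1.96) = 84.4%.

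| R² | 1/k | True type I error, strata omitted | Power omitted / included, rho = 0 | Gap (points) | Power omitted / included, rho = 0.5 | Gap (points) |
|---|---|---|---|---|---|---|
| 0 | 1.00 | 5.0% | 80.5% / 80.5% | 0 | 90.3% / 90.3% | 0 |
| 0.02 | 1.01 | 4.8% | 80.8% / 81.3% | 0.5 | 90.5% / 90.8% | 0.3 |
| 0.05 | 1.03 | 4.4% | 81.1% / 82.5% | 1.3 | 90.8% / 91.6% | 0.8 |
| 0.10 | 1.05 | 3.9% | 81.8% / 84.4% | 2.7 | 91.4% / 93.0% | 1.5 |
| 0.20 | 1.12 | 2.8% | 83.2% / 88.4% | 5.2 | 92.6% / 95.4% | 2.7 |

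Gaps are taken before rounding the powers.

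**Simulation check.** There were 3,000 trials per setting, each with 260 participants in 12 strata, assumed permuted blocks of 4, assumed stratum frequencies and 20% random dropout. No stratification factor reached p < 0.05 at T0 in any trial. With T0 BDI-II in the model and the strata omitted, the rejection rate under no effect at R² = 0.20 was 3.9% for rho = 0 and 3.0% for rho = 0.5, against 2.8% by formula. Dropout and incomplete blocks undo part of the balance, so the formula is best read as the far end of the conservatism. Simulated power at rho = 0.5 was 90.2% against 91.2% (R² 0.05), 90.3% against 92.2% (0.10) and 90.9% against 94.4% (0.20), in line with the table given simulation error.

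**The case against.** **Silence is not exclusion.** This is a condensed article, and a full covariate list is commonly left to the analysis plan, which is not shown. For the mixed models this stands. A reader might infer that they leave the strata out, but the text mentions only a random intercept and does not list fixed-effect covariates, so it supports neither reading. For the ANCOVA the objection fails, because the article states a positive rule. An analysis plan that followed the rule would leave the factors out, and one that named them would depart from the rule.

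**The rule may govern only sensitivity analyses.** This stands as an ambiguity. The sentence ends with those words, and it is unclear whether they apply to all the covariates or only to the extra characteristics. On neither reading is a stratification factor named for the primary model. The ambiguity has a larger consequence elsewhere: whether T0 BDI-II is in the primary ANCOVA moves power from about 80% to about 90% at an assumed correlation of 0.5, more than the strata do.

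**Power is not lost.** A reader might infer that the trial falls short of its planned 80%, or might set the adjusted power of 82%, 84% or 88% against a fixed 80%. The article does not support either. The trial is sized on an unadjusted t-test, and under stratified allocation the analysis without strata itself has about 81% to 83% power at R² of 0.05 to 0.20. Only the gaps in the table are forgone.

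**The size rests on an assumed R².** This stands. BAI class in particular may overlap with T0 BDI-II, and only what the strata add beyond it counts. At 0 to 0.02 the effect is negligible.

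**Conclusion.** The point holds for the ANCOVA and is modest in size. The written rule in effect bars the factors on which the trial is stratified. If they are prognostic beyond T0 BDI-II, the reported standard error is too large by about 1% to 12% for R² of 0.02 to 0.20. At R² of 0.05, 0.10 and 0.20 the true type I error is about 4.4%, 3.9% and 2.8%. Relative to an adjusted analysis, about 1 to 5 points of power are forgone without baseline adjustment, and about 1 to 3 points with T0 BDI-II in the model at an assumed correlation of 0.5. If the factors are not prognostic, nothing is forgone.

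The error is conservative: type I error is not inflated and the planned 80% is kept. These sizes rest on assumed values of R² and the correlation, and on near-exact balance in the analysed sample. For the mixed models the conclusion goes no further than that their covariates are not stated.

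**What to change.** In the Statistical analysis section, and in the analysis plan:

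1. Name T0 BDI-II, gender, BAI class (two levels) and IPAQ-SF level (three levels), coded as used for stratification, as fixed covariates in the primary T1 ANCOVA, whatever their observed balance.
2. State that the linear mixed models include the same stratification factors.
3. Drop the rule that selects covariates by a significant difference at T0. Any further covariates for sensitivity analyses should be listed in advance.
4. Reword the ANCOVA sentence so that T0 BDI-II is plainly in the primary model.

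The cost is wording and 1 + 1 + 2 = 4 degrees of freedom of roughly 208 (2 × 104). The three stratification factors must be known before randomisation and T0 BDI-II is already collected at baseline, so no new data are needed and the sample size does not change.
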